**Figure 1 F1:**
[figure not shown]
Study design. The design of the study, showing the measurement points and the conditions.

### Study procedures

The baseline measurement will be split to reduce the burden on participants. One part of the baseline measurement will be conducted immediately after obtaining informed consent (i.e., general questions, inclusion and exclusion criteria, MINI-S, LEC-5, CAPS-5-R, VLGT and hair sample; see table 1). The self-report questionnaires of the baseline measurement are filled out separately, at home, with a research team member present online for questions and completeness of the data.

Consequently, participants are randomly assigned to either M-TFT or S-TFT in a parallel design. The random assignment is carried out on a 1:1 basis using Castor EDC, which incorporates blocked randomisation of 2, 4 and 6, stratified by location. A research associate employed by the sponsor who is not otherwise involved in the study will assign patients to their respective treatment.

Informed consent and the first part of the baseline measurement will take place at a participating centre; all other assessments will take place in online meetings (T1–T4). Assessments will be conducted by psychologists and master’s-level psychology students who have received training in all assessment procedures and instruments. Outcome assessors will administer all clinician-rated instruments blind to treatment conditions. To enhance participant retention, participants will receive €25 if they complete the measurement at T4.

### Analyses

#### Descriptive statistics

We will provide descriptive statistics including demographic variables (age, gender, education level and country of origin) and trauma-related variables (number of PTEs and trauma background). Variables will be tested for differences between treatment completers and drop-outs.

#### Clinical effectiveness

For the primary clinical outcome, repeated measurement analyses using linear mixed models (LMM) will be used to study changes over time in clinician-rated PTSD symptom severity as measured with the CAPS-5-R. We will assess differences in response patterns between the groups. In addition, we will test the difference between the two groups by running a customised test within the LMM at the 9-month time point and base our decision to declare non-inferiority on the corresponding 95% CI. The linear mixed model will compute estimates for missing data. In addition, disaggregated analyses of the primary outcomes will be conducted for gender and trauma background (profession-related vs other). All the analyses above will be carried out on an intent-to-treat basis.

#### Cost-effectiveness analysis

A cost-utility analysis (CUA) will be performed. Cost-utility will be calculated as the difference in mean costs and the difference in QALYs between treatments, yielding a cost per QALY estimate. Societal costs will be valued using reference prices from the Dutch manual for costing in economic evaluations.^49^ Societal costs and QALYs will be modelled for the CUA using generalised linear models (GLM). In addition to calculating the incremental cost-utility ratio (ICUR), an incremental net benefit analysis will be conducted. This approach directly incorporates willingness-to-pay (WTP) thresholds to estimate the net benefit for each treatment. Probabilistic sensitivity analyses will be performed and uncertainty will be visualised using cost-effectiveness acceptability curves (CEACs), which plot the probability that a treatment is cost-effective across a range of WTP thresholds. SEs around the GLM coefficients will be used to explore uncertainty using non-parametric bootstrapping. Cholesky decomposition will be applied to retain the correlations between parameters. Results will be presented in the cost-effectiveness plane and through CEACs to estimate the probability that one treatment is more cost-effective.

### Secondary analyses

For the secondary study parameters, multiple imputations will be applied to missing data. Hierarchical regression analyses will be performed to examine potential predictors of PTSD treatment outcomes and moderators of the relationship between treatment outcome and condition. For this, we will use the severity of comorbid disorders, dissociation, experiential avoidance, social support, verbal memory, trauma background and cortisol at pretreatment. We will correct for multiple tests.

We also intend to calculate a Personalised Advantage Index (PAI). We will use leave-one-out cross-validation to generate the counterfactual prediction per patient using prognostic and prescriptive variables from moderation analyses and generate the PAI, the magnitude of the predicted difference of receiving the predicted optimal treatment versus the non-optimal treatment.^50^ For the trees for treatment-subgroup interactions, we will use the R package quint.

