Even though M-TFT has potential benefits over S-TFT, the current Dutch treatment guidelines for PTSD only recommend M-TFT after patients have shown an insufficient treatment response to two evidence-based interventions of S-TFT.^8^ Consequently, treatment may become unnecessarily prolonged and cost-ineffective, especially in multiply traumatised patients. A previous study comparing the cost-effectiveness of M-TFT and S-TFT in patients with childhood abuse-related PTSD^17^ found a small but significant difference of 0.027 in quality-adjusted life years (QALYs) in favour of massed treatment. As PTSD results in an average of 15.2 additional days of absenteeism,^3^ the cost-effectiveness of M-TFT might be higher in employed patients due to a faster reduction in absenteeism. Conducting M-TFT as a first-line treatment for PTSD might therefore reduce societal costs related to PTSD.

This paper describes the study protocol for a multicentre, parallel (1:1), single blinded, RCT of M-TFT versus S-TFT as First-Line Intervention for PTSD - Intensive Treatment, using the acronym FLIP-IT. The primary aim of the trial is twofold: (1) to investigate whether M-TFT is non-inferior to S-TFT in reducing PTSD symptoms in employed patients who have been exposed to multiple potentially traumatic events (PTEs) and who seek first-line treatment for PTSD and (2) to investigate the clinical and cost-effectiveness of M-TFT versus S-TFT. Following the literature, we hypothesise that while long-term effectiveness is comparable to S-TFT, M-TFT’s higher session frequency leads to faster symptom relief,^13^,^16^ enhancing patients’ quality of life and leading to lower societal costs.^17^

Secondary aims concern investigating differential effects on drop-out and identifying predictors and moderators of treatment outcome. We hypothesise that M-TFT has lower drop-out than S-TFT. In line with previous research, we also hypothesise that comorbid disorders, dissociation, experiential avoidance, verbal memory, trauma background and cortisol levels are negative predictors of treatment outcome in both conditions, while social support is a positive predictor.^2^ Last, through qualitative analysis, we aim to understand who may benefit most from M-TFT versus S-TFT and how to improve its application.

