### Sample size calculation

The sample size calculation is based on the upper endpoint of the 95% CI for the difference in mean change scores from baseline to 9 months between M-TFT and S-TFT (adjusted for baseline) being less than the margin of seven CAPS-5 points (not the revised version). As the CAPS-5-R is backwards compatible with the CAPS-5,^22^ we drew from the extant RCT data examining evidence-based PTSD treatment using the CAPS-5. These treatments vary in their minimal change range from 7 to 10 CAPS-5 points, with an SD of 15.6 points.^13^ With a 5% significance level and 80% power, a total sample of 124 participants (62 in both conditions) is needed to detect non-inferiority when M-TFT is truly non-inferior to S-TFT using a 7-point difference on CAPS-5. The sample size was increased to 186, based on the 33% expected drop-out at the last assessment point at 9 months (figure 1).

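### The variable list for the predictor regressions leaves out baseline CAPS-5-R, so severity-type measures could pass as predictors merely by tracking initial PTSD severity

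*Protocol article*

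**What the plan says.** The Introduction sets a directional hypothesis for a secondary aim: "comorbid disorders, dissociation, experiential avoidance, verbal memory, trauma background and cortisol levels are negative predictors of treatment outcome in both conditions", with social support as a positive predictor. Baseline PTSD severity is not named there.

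The Secondary analyses section gives the method: "Hierarchical regression analyses will be performed to examine potential predictors of PTSD treatment outcomes and moderators of the relationship between treatment outcome and condition". It then names the variables: "we will use the severity of comorbid disorders, dissociation, experiential avoidance, social support, verbal memory, trauma background and cortisol at pretreatment". It adds "We will correct for multiple tests", without naming the correction. It does not give the contents of the blocks. It also does not say whether the outcome is the follow-up score, the change from baseline or something else.

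Baseline CAPS-5-R is available for every participant. Table 1 schedules it at T0, and Study procedures places it in the first part of the baseline visit, before randomisation ("inclusion and exclusion criteria, MINI-S, LEC-5, CAPS-5-R, VLGT and hair sample"). The article does mention baseline adjustment in one other place: the contrast in Sample size calculation is described as "adjusted for baseline) being less than the margin of seven CAPS-5 points".

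**The concern.** Several of the listed domains are measured with symptom scales, such as the HADS for anxiety and depression, a dissociation scale and an avoidance questionnaire. It is reasonable to expect these scores to be higher in people whose PTSD is worse at entry, and initial severity usually carries through to later severity in part. A model without initial severity cannot tell a variable that adds information from one that only restates how ill the participant was at the start.

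The direction of the error is the more awkward part, because the hypothesis is directional. Scored as the follow-up value, shared severity pushes a variable towards predicting a worse result. Scored as raw change, regression to the mean pushes the same variable towards predicting greater improvement. The same data could then support or contradict the hypothesis depending on a scoring choice that the article leaves open. The planned multiplicity correction does not help, because it controls chance and not confounding.

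**Working it through.** The article states no figure for these regressions, so there is none to reproduce. The check asks how often a variable with no effect of its own would be declared a predictor.

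**Inputs**
- From Sample size calculation: 124 evaluable participants at 9 months and 186 randomised, with 33% drop-out (186 × 0.67 = 124.6). Multiple imputation is planned for the secondary parameters, so both sizes were run.
- Assumed, because the article gives no correlations: a = correlation of the predictor with baseline CAPS, 0.2 to 0.5; r = correlation of baseline with 9-month CAPS, 0.3 to 0.5; equal variances at both times; one predictor at a time; two-sided 5% test.

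**Formulas for a predictor without its own effect**
- Induced correlation with the follow-up score: a × r.
- Induced correlation with change (follow-up minus baseline): (a × r − a) / √(2 − 2r).
- Example, a = 0.5 and r = 0.3: follow-up 0.5 × 0.3 = 0.15; change (0.15 − 0.50) / √1.4 = −0.296.

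**Simulated rejection rates, n = 124, 2,000 trials per setting**

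| a | r | Induced correlation, follow-up | Induced correlation, change | Rejected, follow-up | Rejected, change | Rejected, baseline in model |
|---|---|---|---|---|---|---|
| 0.2 | 0.3 | 0.06 | −0.118 | 11% | 27% | 6% |
| 0.2 | 0.5 | 0.10 | −0.100 | 20% | 21% | 5% |
| 0.3 | 0.3 | 0.09 | −0.177 | 17% | 51% | 5% |
| 0.3 | 0.5 | 0.15 | −0.150 | 37% | 37% | 5% |
| 0.5 | 0.3 | 0.15 | −0.296 | 38% | 92% | 5% |
| 0.5 | 0.5 | 0.25 | −0.250 | 81% | 80% | 5% |

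At n = 186 the ranges are 13–93% (follow-up) and 28–99% (change), so more data makes the problem worse. A separate simulation with treatment condition in the model gave nearly the same rates (for example 17% and 50% at a = r = 0.3).

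**Hand check and multiplicity.** At a = 0.4 and r = 0.5 the induced correlation is 0.20. With n = 124 the expected t is 0.20 × √122 / √(1 − 0.04) = 2.25. The chance of exceeding 1.98 is then about 61% (simulated: 63%). A seven-test Bonferroni threshold of about 2.75 still leaves about 31% (simulated: 32%).

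**Why adjustment settles the scoring question.** Once baseline is a covariate, subtracting baseline from the outcome lowers the baseline coefficient by 1 and leaves the predictor's coefficient and its test unchanged. Adjustment also cuts residual variance by r²: 0.3² = 9% to 0.5² = 25%.

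**Moderators.** With n = 186, a = r = 0.5, baseline omitted and no moderation by baseline severity, the predictor-by-condition test rejected in 5.2% of trials, which is nominal.

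**The case against.** The strongest reply is that the sentence lists candidates, not the whole model. Treatment condition is missing from it too, yet no moderator model can be fitted without condition. Hierarchical regression means entry in blocks, and an earlier block could hold baseline CAPS-5-R. A condensed article commonly leaves block contents to the full protocol or analysis plan, and the phrase in Sample size calculation shows that the authors know about baseline adjustment. This stands to the extent that omission from the fitted model is not shown. A reader might infer that the trial will run unadjusted models; the article does not establish that. What remains is that the article does name the variables to be used, and the one that matters most for reading the others is not among them.

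A second reply is that the hypothesis speaks of predictors, not of predictors independent of initial severity. A scale that correlates with the follow-up score does predict it. That is fair for the follow-up score. It does not rescue the raw-change reading, where the same scale would point the other way.

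Third, the size is assumed throughout. Other severity scales entered together would absorb part of the effect, and requiring a PTSD diagnosis at entry may narrow the baseline spread and weaken the correlations. The sign reversal also depends on the variances: covariance with change is proportional to r × (follow-up SD / baseline SD) − 1. At r = 0.5 this is −0.50 with equal SDs but 0.5 × 1.5 − 1 = −0.25 with a ratio of 1.5. All of this stands, and the rates should be read as illustrations.

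**Conclusion.** The point holds in a narrow form. As listed, the main-effect predictor regressions cannot separate comorbidity, dissociation and avoidance from initial PTSD severity, and the direction of the resulting bias depends on an outcome scoring that the article does not state. Under the assumed correlations, the chance of a spurious predictor is about 11–81% (follow-up score) or 21–92% (change) at n = 124, against about 5% after adjustment. The reversed direction for change assumes similar variances at baseline and follow-up.

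Three stronger readings are tempting but unsupported. A reader might infer that moderator findings are equally confounded; randomisation protects the interaction tests unless baseline severity itself moderates the treatment effect. A reader might infer that the Personalised Advantage Index is biased; it is a prediction tool, a variable that tracks severity still predicts, and the loss is precision at most. A reader might infer that the non-inferiority conclusion is affected; the primary test and the sample size do not depend on these models. This is an inexpensive improvement to a secondary analysis.

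**What to change.** In Secondary analyses, state that each predictor regression uses follow-up CAPS-5-R as outcome, with baseline CAPS-5-R and treatment condition in the first block and the listed variables after them. Include baseline CAPS-5-R as a covariate in the moderator models and in the outcome model behind the Personalised Advantage Index. A baseline-by-condition term in the moderator models is optional; it guards against a claimed moderator standing in for initial severity. If the full protocol or analysis plan already does this, one sentence saying so is enough.

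The cost is wording and about one degree of freedom per model (one more if the optional term is used). Some variables will look weaker once initial severity is accounted for. No new data are needed and the sample size does not change.

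### As written, leave-one-out for the Personalised Advantage Index covers the prediction but not the choice of moderators, so any matching benefit built on a chance moderator is biased upward

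*Protocol article*

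**What the plan says.** The Secondary analyses section of the protocol article sets out two steps. First: "Hierarchical regression analyses will be performed to examine potential predictors of PTSD treatment outcomes and moderators". The candidates are "the severity of comorbid disorders, dissociation, experiential avoidance, social support, verbal memory, trauma background and cortisol at pretreatment", and the section adds: "We will correct for multiple tests".

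The PAI follows as an intended further analysis: "We will use leave-one-out cross-validation to generate the counterfactual prediction per patient using prognostic and prescriptive variables from moderation analyses". The index is defined as "the magnitude of the predicted difference of receiving the predicted optimal treatment versus the non-optimal treatment".

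The section gives no threshold for entering a variable into the PAI and does not say whether the multiplicity correction governs that entry. It mentions neither a data split nor selection repeated within each left-out fit. The Introduction lists "identifying predictors and moderators of treatment outcome" among the secondary aims.

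**The concern.** Leave-one-out gives an honest prediction only if the held-out patient had no part in building the model. Here the variables are an output of the moderation analyses, and leave-one-out is attached to the prediction step alone. If the moderation analyses use all patients, each patient's outcome helps decide which interactions enter. Refitting the coefficients without that patient does not undo this. An interaction that arose by chance in these data will tend to predict well in the same data, held out or not.

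The trial wants to learn who does better on massed and who on spaced treatment. A chance moderator carried into the PAI could be reported as a cross-validated personal advantage. The definition of the index adds to this: a magnitude cannot be negative, so it is above zero even when no moderation exists.

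**Working it through.** **Inputs from the protocol article.** Sample size calculation: "a total sample of 124 participants (62 in both conditions) is needed"; "The sample size was increased to 186, based on the 33% expected drop-out"; SD 15.6 and margin 7, both in CAPS-5 points. Secondary analyses: seven candidate domains. Allocation is 1:1.

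**The plan's own figure.** It gives none for the PAI, so the sample size is reproduced because it sets N.
- Per arm: 2 × (1.645 + 0.842)² × 15.6² / 7² = 61.4, so 62 per arm and 124 in all (one-sided 5%, 80% power).
- With drop-out: 124 / 0.67 = 185.1, so 186.

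**Assumptions not in the document.** Independent normal candidates, one of them prognostic (r = 0.3); no treatment effect; no true moderation; 7 candidates (12 as an upper variant, since a domain may have several scales); a range of entry thresholds.

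**How often a chance moderator enters.** With 7 independent tests at level a, the probability is 1 − (1 − a)⁷. The simulated rates agree with it.

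**What follows when one enters.** Each candidate's interaction was tested on all 124 patients, and the chosen ones were fixed and refitted leave-one-out. Benefit is the mean outcome of patients on their predicted non-optimal arm minus that of patients on their predicted optimal arm. Its true value is zero.

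| Entry threshold | 1 − (1 − a)⁷ | Selected in simulation | Mean benefit if selected (points) | Positive if selected | Falsely significant, all trials |
|---|---|---|---|---|---|
| 0.05/7 (Bonferroni) | 4.9% | 5.5% | 6.3 | 100% | 3.9% |
| 0.05 | 30.2% | 31% | 4.8 | 99.6% | 10.7% |
| 0.10 | 52.2% | 51% | 4.4 | 98.6% | 15.5% |
| 0.20 | 79.0% | 79% | 3.9 | 96.8% | 17.9% |

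In SD units, 4.4 / 15.6 = 0.28 and 6.3 / 15.6 = 0.40. If trials without a selected moderator count as zero, the averages over all trials are 0.055 × 6.3 = 0.3 points (Bonferroni), 0.31 × 4.8 = 1.5 (p<0.05) and 0.51 × 4.4 = 2.2 (p<0.10).

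**Is selection outside the loop the cause?** Two comparisons say yes.
- All 7 candidates kept, no selection, leave-one-out: mean benefit 0.0 points, 4.2% falsely significant.
- Selection repeated inside each training fold (10-fold), in trials where the full sample selects a moderator:

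| Threshold | Mean benefit, outside → inside folds | Falsely significant in all trials, outside → inside |
|---|---|---|
| 0.05 | 4.7 → 1.3 | 11.2% → 3.1% |
| 0.10 | 4.3 → 1.1 | 15.5% → 5.8% |
| 0.20 | 3.7 → 0.6 | 17.2% → 5.8% |

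A check with leave-one-out folds at p<0.10 also gave about 1.1 points. That remainder comes from averaging only over trials in which the full sample had picked something; without that condition the nested estimate averages about zero. With nested leave-one-out, a simple t-test still rejected somewhat more often than its nominal 5% at uncorrected thresholds, which is one reason for a permutation reference.

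**Sensitivity.** With 12 candidates at p<0.20, a moderator is selected in 93% of null trials (1 − 0.8¹² = 93%) and 31% of all trials are falsely significant. At N = 186 the rates are similar and the mean benefits smaller, about 3.1 to 5.2 points.

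**The index itself.** The mean absolute PAI with no true moderation was about 4.5 to 8.6 points across the settings.

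**The case against.** Four objections deserve weight.

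1. The article announces a correction for multiple tests just before the PAI. If it governs entry, a chance moderator is rare (about 4 to 6% of null trials) and a falsely significant benefit rarer still (3.9%). This stands as a limit on frequency. But the text does not tie the correction to PAI entry, and in the few trials where a moderator passes it the spurious benefit is largest (6.3 points).

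2. The article never says that selection uses the full sample. It condenses a fuller protocol and cites a method source, neither shown, and nesting might be specified there. This stands in part, and the point therefore rests on the plain reading. It is still more than missing detail, because the article names both where the variables come from and which step is cross-validated, and that combination is biased if followed.

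3. No comparison of observed outcomes between predicted optimal and non-optimal arms is announced. This stands: the benefit figures describe a validation step that commonly accompanies a PAI but is not stated here. The index that is stated has its own difficulty, since a magnitude is positive without any moderation.

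4. The analysis is secondary and exploratory. This stands and sets the priority.

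A reader might go further and infer that the PAI will show a matching benefit even if none exists. The documents do not support that: with no moderator selected there is no such benefit to report, and that happens in roughly half of null trials at p<0.10 and nearly all of them under Bonferroni.

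**Conclusion.** The point holds in conditional form. On the plain reading of the Secondary analyses section, variable selection sits outside the cross-validation. Whenever a moderator is then selected by chance, any apparent matching benefit is biased upward, by about 4 to 6 CAPS-5 points on average for thresholds from p<0.10 down to Bonferroni, against a margin of 7. How often this happens ranges from about 4–6% to about 50% of null trials over the same thresholds, and the article does not fix which applies.

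The sizes rest on independent normal candidates, 7 scales, N = 124 and SD 15.6. They are in CAPS-5 points, as in the sample size calculation; the trial itself scores the CAPS-5-R. The direction of the bias does not depend on these choices. This should be corrected before analysis, but it does not bear on the non-inferiority or cost-utility results.

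**What to change.** State in the analysis plan one of two routes:

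- repeat predictor and moderator selection, together with imputation and model fit, inside every training fold; or
- prespecify the PAI variables and keep them all, without data-driven selection.

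Under the first route, state the entry threshold and whether the multiplicity correction applies to it. Under either, report any optimal versus non-optimal difference only from the held-out predictions. Because the index is non-negative by construction, show it beside a permutation or other null reference.

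The cost is analysis code and some extra computing, and the reported advantage will probably be smaller. No data collection changes, and with inclusion planned until July 2027 there is time to settle this before analysis.
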